#### Oral cognitive test battery

At four time points, participants will undergo an oral cognitive test battery consisting of seven tests that were validated for repeated use in people with SCI, even with impaired hand function [43]. The Dutch version of these tests will be used, whenever the test depends on language. The tests have a good-to-excellent test–retest reliability, except the RAVTL recognition score which has been shown to have a poor test–retest reliability [43]. This test was still used as the interference recall and delayed recall scores of this test have a good test–retest reliability in people with SCI [43]. To further decrease learning effects of repeated administration of the cognitive tests, different versions will be used on different visits if available. The test versions will be numbered and on their first visit participants will be asked to draw a random number from an envelope including a number for every existing version of the cognitive test, until the envelope is empty. This is repeated for every cognitive test. The sequence will be reported for the next visits. The cognitive tests are presented in Table 1.

**Table 1 Tab1:** Oral cognitive assesments

Cognitive test	Description

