#### Study procedures

The experimental design is illustrated in Fig. 1. Upon the first appointment (T1), participants will sign an informed consent and undergo baseline examinations consisting of questionnaires and clinical tests. A smartphone application for repeated monitoring of cognitive function will be installed on their smartphones and they will be familiarized with the cognitive tests and neuromuscular electrical stimulation intervention. On a separate day (T2), within seven days from the first appointment, they will undergo a series of cognitive tests and venous blood samples will be collected. Furthermore, they will fill in a second list of questionnaires and undergo a clinical evaluation of strength and spasticity. This will be followed by a no-treatment baseline period with a random length of 3–8 weeks. Upon the third (T3), fourth (T4) and fifth (T5) visit, the oral cognitive tests, venous blood sample collection and questionnaires from T2 will be repeated. During the third visit (T3) the participants will receive their own NMES device for home-based training and they will be asked to return it 12 weeks later on the fourth visit (T4). All participants will undergo the same intervention. During the fourth visit (T4) the clinical evaluation of strength and spasticity that was done at T2 will be repeated. Between T2 and T4 and between T5 and T6 participants will undergo smartphone cognitive tests 3 times per week. At the end of the study, no additional tests will be done. Participants will be requested to write in a diary the specifications of the NMES session (duration, intensity) after each session and indicate when they performed a cognitive test. They can also write down any problems they encountered using the NMES device or smartphone application. Participants receive a telephone call once a week by one of the researchers to assess how they feel, be reminded of the diary and to assure there are no technical issues with the NMES device or smartphone application. Participants are allowed to withdraw from the study at any time. Available data from these participants will be included in the data analyses whenever possible.

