**Information processing speed**	
SDMT	This test is similar to the m-Path smartphone test. However, now, the participant is asked to verbally match the number representing the symbol given as depicted in the legend provided on the top of the page. The researcher writes down the answers on a separate page. The first 10 trials are used for familiarization, then the participant is given 90 s to verbally match as many numbers to symbols as possible. The final score is obtained by subtracting the number of errors from the number of items completed within the given timeframe [34]. To minimize learning effects, three different versions of this test will be used

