**Verbal fluency**	
COWAT	For this test participants are asked three times to name as many words starting with a specific letter in one minute time. Words cannot be named more than once and non-existing words are not counted. In addition, names of persons and numbers are also not allowed. There are three versions of this test (DAT, KOM, PGR) in the Dutch language. The total score is the sum of the number of words named for each of the three letters [34, 35]

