**Memory**	
15 word test (RAVLT)	The 15 word test is the RAVLT. This test consists of a list of 15 words that is read to the participant by an assessor. After reading, the participant must try to recall as many words as they can. This read and recall process is repeated an additional four times. A distractor list (second list) is presented with a recall attempt, followed by a timed recall of the first list. The timed recall measures the participant’s ability to recall information despite the intervening list. After 10 min, the participant performs another timed recall of the first list of words. Afterwards the participant is given a recognition task where they identify the 15 words from the initial list from a paragraph containing 30 underlined words. This final trial distinguishes memory storage from inefficient recall [34]. There are two versions of this test available at our institution

Abbreviations: *COWAT* controlled word association test, *RAVLT* Rey Auditory Verbal Learning Test, *SDMT* Symbol Digit Modalities Test, *TMT* Trail Making Test

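### For the RAVLT and both digit spans, the envelope draw puts the first repeat of test material at T4 in every participant, so any re-exposure gain is fully confounded with the NMES interval

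*Protocol article*

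**What the plan says.** The protocol article (Oral cognitive test battery) states: "At four time points, participants will undergo an oral cognitive test battery consisting of seven tests". Study procedures places the first administration at T2 and the repeats as follows: "Upon the third (T3), fourth (T4) and fifth (T5) visit, the oral cognitive tests". The NMES device is handed out at T3 and returned 12 weeks later at T4.

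To limit learning, the same section says that "different versions will be used on different visits if available". On the first visit participants "draw a random number from an envelope including a number for every existing version of the cognitive test, until the envelope is empty", separately for each test, and "The sequence will be reported for the next visits". No rule is given for visits after the envelope is empty.

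Table 1 gives the number of versions:
- RAVLT, Digit Span Forward and Digit Span Backward: two each ("There are two versions of this test available at our institution").
- SDMT: "three different versions of this test will be used".
- COWAT: "There are three versions of this test (DAT, KOM, PGR) in the Dutch language".
- Stroop: one.
- TMT: number not stated.

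The battery is a secondary outcome in a single-armed design, analysed by a Friedman test with false discovery rate correction (Secondary statistics).

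**The concern.** The draw randomises which version comes first. It does not randomise when repetition begins. With two versions, repetition begins at T4 for everyone, and T4 is the post-intervention visit.

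This arm has no control group, so the untreated T2-to-T3 interval is its only internal guide to practice. For two-version tests that interval goes from new to new material. It can show general familiarity with the task, but not the advantage of meeting the same word list or digit strings again. T3 to T4 goes from new to seen material in every participant, so no later analysis can separate the two explanations.

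The RAVLT is the most exposed. It is the battery's only memory test, and its list is read and recalled five times, recalled again after a distractor list and after a delay, and then used in a recognition task. At stake is whether a T3-to-T4 improvement in memory or attention scores can be credited to NMES at all.

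**Working it through.** **The plan's own figure.** Sample size calculation gives a minimum of 7 for the time effect over four visits. Inputs: d = 0.71, so f = 0.71/2 = 0.355; m = 4 visits; correlation 0.77; power 0.80; alpha 0.05 assumed. The noncentrality is n·m·f²/(1 − ρ), with 3 and 3(n − 1) degrees of freedom.
- n = 6: 6 × 4 × 0.126 / 0.23 = 13.2, power 0.766.
- n = 7: 7 × 4 × 0.126 / 0.23 = 15.3, power 0.850.

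The figure of 7 is reproduced. The point here does not depend on it.

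**Counting versions.** All sequences over T2 to T5 were enumerated: draw without replacement until empty, then any re-use.

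| Test | Versions | T2 | T3 | T4 | T5 |
|---|---|---|---|---|---|
| RAVLT, Digit Span Forward, Digit Span Backward | 2 | new | new | seen | seen |
| SDMT, COWAT | 3 | new | new | new | seen |
| Stroop | 1 | new | seen | seen | seen |
| TMT | not stated | – | – | – | – |

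This holds with probability 1 under any re-use rule. At T4 a two-version test repeats either the T3 version (12 weeks earlier) or the T2 version (3 + 12 = 15 to 8 + 12 = 20 weeks earlier).

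**Illustrating the size.** The documents give no gain from re-exposure after 12 to 20 weeks, so a range is assumed. Simulation: n = 15, correlation 0.77, no NMES effect, gain g (in SD) added whenever a version is met again, two-sided 5%, no FDR adjustment. Under the envelope rule the mean pattern over T2 to T5 is 0, 0, g, g. With sequences AABB, BBAA, ABAB and BABA, about half the participants follow 0, g, 0, g and half 0, 0, g, g, so the mean pattern is about 0, g/2, g/2, g.

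| Rejection rate | g = 0.2 | g = 0.3 | g = 0.5 |
|---|---|---|---|
| Envelope, Friedman (planned) | about 18% | about 36% | about 83% |
| Envelope, Wilcoxon T3 vs T4 | about 18% | about 34% | about 74% |
| Balanced list, Friedman | about 10% | about 18% | about 43% |
| Balanced list, Wilcoxon T3 vs T4 | about 5% | about 3% | about 2% |

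With g = 0 both tests reject in about 4% to 5%. For a three-version test under the envelope rule, T3 versus T4 stays at about 5%, but the repeat at T5 raises the Friedman rate to about 13%, 27% and 67%.

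**If memory fades.** Under AABB the repeat at T3 comes after 3 to 8 weeks; under ABAB the repeat at T4 comes after 15 to 20 weeks. With assumed gains of 0.5 SD (short) and 0.2 SD (long), the mean T3-to-T4 change under even balance is (−0.5 + 0.2)/2 = −0.15 SD. With an 8/7 split it is (8 × −0.5 + 7 × 0.2)/15 = −0.17 SD. Either way the bias runs against NMES.

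**The case against.** Several objections have force.

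- **The gain is assumed.** Nothing in the protocol supports 0.2 to 0.5 SD after 12 to 20 weeks, and carry-over is far less plausible for digit strings than for a rehearsed word list. This stands. The design is confounded; a bias has not been demonstrated.
- **The protocol foresees a shortage.** It promises different versions only where available, and says the tests were validated for repeated use in SCI. But the proviso does not say where repeats should fall, and the stated draw fixes that at T4. The support offered is test–retest reliability, which is compatible with a uniform mean gain.
- **The envelope has a merit.** For two-version tests it keeps each version's first repeat at least 12 weeks from its last exposure. A balanced list makes about half the participants repeat a version after 3 to 8 weeks. This stands as a real trade-off. If long-interval memory is very weak, the list can do worse: with 0.5 SD short and 0.1 SD long, the T3-to-T4 Wilcoxon test rejects in about 16%, against about 8% under the envelope, though in the direction against NMES.
- **Balancing does not cure the planned test.** T2 stays all new and T5 all repeated, so the excess in the Friedman test is only about halved. This also stands.

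A reader might infer that the whole battery is compromised at T4. The documents do not support that: SDMT and COWAT do not repeat until T5, Stroop already repeats from T3, and the TMT number is not given.

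**Conclusion.** The point holds for the RAVLT and both digit spans. That the first repeat falls at T4 in every participant is certain from the protocol's own counts, and it coincides with the NMES interval in an uncontrolled arm. The T2-to-T3 change cannot correct for it. For SDMT and COWAT the equivalent issue arises only at T5.

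The size is conditional. The percentages rest on assumed gains, n = 15, correlation 0.77 and unadjusted tests. They show that a modest gain would be enough to matter, not that such a gain will occur. The concern is strongest for the RAVLT word list.

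Two stronger readings should be resisted. A reader might conclude that remembered items will produce a false NMES effect; the protocol contains nothing on the size of item memory over these intervals. A reader might also conclude that the trial's main result is at risk; the smartphone test is the primary endpoint, does not use these versions, and is unaffected.

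**What to change.** For two-version tests, replace the envelope with a prepared list of four-visit sequences that balances whether the first repeat falls at T3 or T4, for example AABB, BBAA, ABAB and BABA allocated as evenly as 15 participants allow. Record repeat status with each score. Base any pre-to-post statement for these tests on the T3-to-T4 contrast shown by repeat status, not on the omnibus Friedman test alone, which stays inflated.

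For SDMT and COWAT, keep three different versions at T2 to T4, state that T5 is a repeat exposure, and do not read T4-to-T5 stability as persistence.

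Cost: one page of allocation, with no extra visits, tests or participants. Downsides to state in the protocol:
- About half the participants repeat a version after 3 to 8 weeks.
- If memory fades with time, the T3-to-T4 change is biased modestly against NMES.
- T2 to T3 then contains some repetition and should not be used unadjusted to correct for practice.
- 15 is not divisible by 4, so balance is approximate.

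If the envelope is kept, the protocol should say that T3-to-T4 gains on the RAVLT and digit spans will not be attributed to NMES.

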**Information processing speed**	
SDMT	This test is similar to the m-Path smartphone test. However, now, the participant is asked to verbally match the number representing the symbol given as depicted in the legend provided on the top of the page. The researcher writes down the answers on a separate page. The first 10 trials are used for familiarization, then the participant is given 90 s to verbally match as many numbers to symbols as possible. The final score is obtained by subtracting the number of errors from the number of items completed within the given timeframe [34]. To minimize learning effects, three different versions of this test will be used
**Verbal fluency**	
COWAT	For this test participants are asked three times to name as many words starting with a specific letter in one minute time. Words cannot be named more than once and non-existing words are not counted. In addition, names of persons and numbers are also not allowed. There are three versions of this test (DAT, KOM, PGR) in the Dutch language. The total score is the sum of the number of words named for each of the three letters [34, 35]
**Attention/concentration**	
Digit Span Forward	Participants will be given a series of numbers, starting with 2 numbers and progressing to 9 numbers, read by an assessor. Participants will be asked to repeat the numbers in the same order. They get two trials before progressing to a larger series of numbers. When both series are answered incorrectly, the test is ended. The total score is the number of correctly answered series [34]. There are two versions of this test available at our institution
**Executive functions**	
Digit Span Backward	This version of the digit span adds a working memory component to the test when compared to the forward digit span. Participants will be given a series of numbers, starting with 2 numbers and progressing to 9 numbers, read by an assessor. Participants will be asked to repeat the numbers backwards. They get two trials before progressing to a larger series of numbers. When both series are answered incorrectly, the test is ended. The total score is the number of correctly answered series [34]. There are two versions of this test available at our institution
TMT A & B	This test assesses switching ability. This test encompasses two parts. In trial A, the participant verbally count from 1 to 25 as quickly as possible. In trial B, the participant will be instructed to verbally alternate between numbers and letters of the alphabet until 13. The time difference between trial A and B will be recorded. This test lasts approximately 3 min [34, 36]
Stroop test	This test assesses cognitive inhibition, but also attention and processing speed. This test consists of three lists that the participant must read out loud; the first list has the names of colors printed in black ink, the second list with the colors printed in colored ink, and the final list having the name of colors printed in incongruent colored ink (e.g., the word red is printed in blue ink). The time to complete second list, third list, as well as the time difference between these latter two lists will be recorded. The test takes approximately 5 min. There is one version of this test available [34, 37]
**Memory**	
15 word test (RAVLT)	The 15 word test is the RAVLT. This test consists of a list of 15 words that is read to the participant by an assessor. After reading, the participant must try to recall as many words as they can. This read and recall process is repeated an additional four times. A distractor list (second list) is presented with a recall attempt, followed by a timed recall of the first list. The timed recall measures the participant’s ability to recall information despite the intervening list. After 10 min, the participant performs another timed recall of the first list of words. Afterwards the participant is given a recognition task where they identify the 15 words from the initial list from a paragraph containing 30 underlined words. This final trial distinguishes memory storage from inefficient recall [34]. There are two versions of this test available at our institution

Abbreviations: *COWAT* controlled word association test, *RAVLT* Rey Auditory Verbal Learning Test, *SDMT* Symbol Digit Modalities Test, *TMT* Trail Making Test

### Blood analysis

Venous blood samples will be taken at the antecubital vein. Blood samples will be collected in two 5 mL serum separator tubes. After blood collection, the tubes will be gently inverted 6–8 times and within 90 min be centrifuged. Quantitative determination of serum BDNF will be measured using enzyme-linked immunosorbent assays (ELISA). Blood will be drawn four times (T2-5) per participant during the whole study project. To decrease errors due to ELISA kit differences, we will store the blood samples in a refrigerator compartment at the Maastricht University laboratory site at -80 °C until analysis, using the same kit for all blood measurements of the same participant at the end of the project.

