Physical exercise interventions have been shown to have anti-inflammatory effects, induce an elevation of neurotrophic factors in the bloodstream, potentiate neuroplastic processes in the brain, increase brain volume and benefit cognitive function [18–21]. The anti-inflammatory effect and increase in neurotrophic factors during exercise results in part from the release of products from contracting muscle cells (i.e. myokines) [20]. This release of myokines has been reported following all sorts of muscle training, including electrical stimulation [20, 22]. It is often difficult for persons with SCI to sufficiently engage in physical exercise, with only 50% of SCI patients engaging in any leisure-time physical activity at all [23]. This difficulty may depend on the level of injury and the severity of motor function loss, as well as the availability of sport opportunities for wheelchair users. Electrical stimulation has been proposed as an interesting addition or alternative for increasing circulating myokine levels in humans with difficulty to participate in regular exercise programs [22]. Electrical stimulation can be used alone, i.e. neuromuscular electrical stimulation (NMES), or to assist voluntary exercise, i.e. functional electrical stimulation (FES). NMES induces contraction of myocytes similarly to exercise, which results in the release of myokines in the circulation, as recently reviewed by Sanchis-Gomar et al. (2019) [22]. A widely studied myokine is brain-derived-neurotrophic factor (BDNF), which is released from neurons [24], astrocytes [25], platelets [26], and skeletal muscle [27] and can trigger neuroprotective and neurotrophic effects [28]. Some studies suggest that most of the circulating BDNF is released from the brain [29]. Some other myokines, like insulin-like growth factor-1 and irisin were suggested to induce the release of brain-derived BDNF [20]. Remarkably, one study in young healthy adults reported that circulating levels of the myokine named BDNF increased more following a single bout of NMES than voluntary exercise with the same integrated force of muscle contraction [30]. Similarly, in a rat study, assessing able-bodied rats, the increase in BDNF levels was two times higher after four weeks of NMES compared to four weeks of running [31]. Also in human studies, long-term interventions with NMES were reported to increase circulating levels of BDNF, for example in older adults with type 2 diabetes [32]. BDNF can be considered one of the most important exercise-induced factors as it has direct beneficial effects on synaptic plasticity and neurogenesis, and it was linked with brain atrophy and cognitive function in a wide array of research [33]. So far, however, we were unable to find any studies reporting a beneficial effect of NMES on cognitive function. To the best of our knowledge, only one other study has evaluated the effects of FES [34] and only one study evaluated the effects of NMES [35] on cognitive function. The FES study is also the only study investigating exercise effects on cognition in SCI patients. In this study, improvements on a working memory task were reported after 6 months of functional electrical stimulation (FES)-assisted rowing exercise in SCI patients. This study did not measure myokine levels [34]. The authors of the NMES study evaluated the effect of a short intervention of 15 days of NMES in coronary bypass patients and discovered that patients in the experimental group showed increases in functional connectivity in the brain frontoparietal, salience and sensorimotor networks [35]. Overall, there is a lack of knowledge on the effects of electrical stimulation to improve cognitive function and the dose–response needed to attain such effect.

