
We will use a randomized replicated ABC single case experimental design (SCED) [36]. Primarily, we will examine to what extent and after how many weeks a 12 week intervention with NMES may change performance of people with SCI on the momentary digital symbol substitution task, an information processing task that will repeatedly be administered via a smartphone application. NMES will be applied to the quadriceps muscles of individuals with SCI. An intervention of 12 weeks is considered to be sufficient to induce both a myokine response and muscular changes. Secondarily, we will assess changes in the myokine BDNF before and after the 12 week intervention with NMES and after a 12 week follow-up without NMES. We hypothesize that NMES will have a beneficial effect on cognitive performance starting from the first weeks and that 12 weeks of NMES will induce an elevation of BDNF levels. This study tests a new treatment strategy, accessible even to individuals with low physical exercise possibilities, with the potential to slow down or prevent further cognitive decline in persons with SCI. The explorative findings may guide future research. Furthermore, it may help to raise awareness of the process of accelerated cognitive decline in persons with SCI.

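### The serum BDNF handling rule sets only a 90-minute upper limit before centrifugation, so clotting time may differ between a participant's visits and add noise to the within-person change

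*Protocol article*

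**What the plan says.** All handling rules are in the protocol article, Blood analysis. The matrix is serum: "Blood samples will be collected in two 5 mL serum separator tubes". The timing rule is "After blood collection, the tubes will be gently inverted 6–8 times and within 90 min be centrifuged". Sampling is repeated: "Blood will be drawn four times (T2-5) per participant during the whole study project". Samples are stored at -80 °C. The one control of measurement error that is explained concerns the assay. It is introduced with "To decrease errors due to ELISA kit differences" and consists of "using the same kit for all blood measurements of the same participant at the end of the project".

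The Introduction describes BDNF as a molecule "which is released from neurons [24], astrocytes [25], platelets [26], and skeletal muscle [27"], and states the aim: "Secondarily, we will assess changes in the myokine BDNF before and after the 12 week intervention with NMES", with a further comparison after follow-up. The Abstract lists BDNF change as a secondary endpoint. Under Secondary data, the design for this endpoint is a single prospective arm. Secondary statistics plans a Friedman test over the repeated measurements, without a term for sample handling.

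**The concern.** Serum is obtained by letting blood clot before it is spun. If platelets are a source of BDNF, part of the measured value may form in the tube after the draw, and the length of the clotting interval may then matter. The rule caps that interval but does not fix it, so two samples from one person can both comply after quite different intervals.

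The endpoint is a difference between such samples in at most 15 people. Variation in handling enters that difference directly, and there is no concurrent control group in which a handling shift between visits would also show up. Matching the ELISA kit within a participant cannot remove a difference that arose before freezing. Data management states that samples are destroyed after analysis, so if times are not recorded the matter cannot be examined later.

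**Working it through.** The plan gives no numerical figure for BDNF variability, expected change or power, so there is nothing of its own to reproduce. Its minimum sample size of 7 concerns the cognitive tests and has no bearing here.

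**What the rule permits.** Upper limit 90 min, no lower limit, no target, the same wording for all four draws. Some time must pass for serum to form, so the usable spread is less than the full 90 min. The calculations below take 30 to 90 min as an assumption.

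**Noise in a change score.** Let the within-person variance per visit be s², and let variable clotting add k·s² per visit, independently between visits.
- Variance of a change without the extra source: 2s². With it: 2s²(1 + k).
- SD ratio: √(1 + k).
- k = 0.25: √1.25 = 1.118, a 12% increase. k = 0.50: √1.50 = 1.225, a 22% increase.

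**What such a k would require.** Suppose log BDNF rises linearly by ln(1 + r) from 30 to 90 min and the delay is uniform over that window. The added SD is ln(1 + r)/√12, and k is its square divided by CV².
- r = 20%, CV 10%: 0.1823/3.464 = 0.0526; k = 0.00277/0.01 = 0.28.
- r = 30%, CV 10%: 0.2624/3.464 = 0.0757; k = 0.00574/0.01 = 0.57.
- r = 30%, CV 20%: k = 0.00574/0.04 = 0.14, and √1.14 = 1.07.
- r = 5%, CV 10%: 0.0488/3.464 = 0.0141; k = 0.00020/0.01 = 0.02, and √1.02 = 1.01.

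So 25–50% corresponds to a fairly strong time dependence together with a small visit-to-visit CV. Weaker dependence or a larger CV gives much less.

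**Effect on the planned test.** Friedman test at nominal 0.05, 15 participants, 4 visits, 20,000 simulated trials per setting, assumed rise of 5–30% between 30 and 90 min. Random delays are uniform over 30–90 min. In the systematic cases, delays are 45 ± 10 min with T4 later by the amount shown.

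| Delay pattern | CV 10% | CV 20% |
|---|---|---|
| Random, false-positive rate | 0.044–0.047 | 0.045–0.046 |
| Random, power for a true 20% rise at T4, from no clotting effect to a 30% effect | 0.99 to 0.92 | 0.54 to 0.48 |
| T4 later by 15 min, false-positive rate | 0.05–0.28 | 0.05–0.10 |
| T4 later by 30 min, false-positive rate | 0.07–0.84 | 0.05–0.30 |

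Random delay costs precision and leaves the type I error alone. Only a delay tied to the visit produces a false group change.

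**The case against.** The strongest objection is that this is laboratory-manual detail. The article condenses a fuller protocol, and a laboratory instruction may already fix the clotting time. That is possible. But the article does state a handling rule, down to the number of tube inversions, and the point is about that rule as fixed. It contradicts nothing in the article, which is why this is a minor improvement and not an error.

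The second objection is that the time dependence is not in the documents. The Introduction names platelets as a source but does not say that release continues in the tube or how fast. This stands, and every size above is therefore conditional.

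A reader might also infer three stronger points that the text does not support:
- That samples from opposite ends of the window are known not to be comparable. The documents give no release rate, so this is a possibility only.
- That transport explains unequal delays, because there are two recruiting locations and one storage laboratory. The article does not say where blood is drawn or spun, or that anyone changes location between visits. A constant difference between locations would lie between participants, and a Friedman test ranks within participants.
- That a BDNF rise will be a handling artefact. This needs a delay that differs by visit. Under Study procedures, T4 includes a strength and spasticity evaluation that T3 does not, which is a conceivable route, but nothing says it delays the spin.

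Nor is there ground to ask for different labelling: the measure is already named as serum BDNF.

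**Conclusion.** The point holds in a limited form. The stated rule bounds the clotting interval from above only, for a serum measurement whose endpoint is a within-person change over four visits without a control group. Unequal intervals within a participant comply with the rule and may add noise to that change. At an assumed added variance of 25–50% of the within-person variance, the SD of a change rises by 12–22%; under weaker time dependence the increase is close to nil. A spurious group-level change would require systematic differences in delay by visit, which the documents neither show nor exclude. The consequence is confined to a secondary endpoint, so this is a low-priority but inexpensive tightening.

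**What to change.** In Blood analysis, or in the laboratory instruction it relies on, replace the bare upper limit by one fixed interval from draw to centrifugation with a narrow tolerance, inside the existing 90 minutes and identical for T2 to T5. The laboratory should choose the value. Record draw and spin time for every sample. With the times on file, a sensitivity analysis can check whether the interval differed by visit and whether the BDNF result changes when it is taken into account.

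The cost is one line of instruction and two recorded times per draw, eight per participant over four draws, plus somewhat less flexibility for whoever handles the tubes. Sample size, visits, assay and primary analysis stay as they are.
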